Finally, preventive strategies against COVID-19 were developed and rapidly disseminated to the Burkinabe population by the media, associations, non-governmental organizations, local elected officials, religious and cultural leaders, and healthcare professionals, without giving a second thought to the acceptability of the measures being promoted for the population. However, the literature as well as media reports indicate that during other epidemics, notably Ebola [27–30], the implementation of preventive strategies (including raising awareness among the population, institutional isolation of infected individuals, collective management of cadavers by specialized healthcare teams) led to misunderstanding and conflictual interpretations between national or international scientific experts, and local populations. This breakdown in communication led to increased mortality, underlining the importance of evaluating the acceptability of preventive strategies for the population in the specific context of Burkina Faso. In addition, several specialists have questioned the feasibility of social distancing and isolation of suspected infected individuals in African populations where the community-based culture prevails. There are also unanswered questions regarding the pathways of care, patient management, and patients’ experiences. The specific objectives of this project comprise three phases, namely:To determine cumulative incidence (i.e., seroprevalence) of SARS-CoV-2 infection in the Burkinabe population (phase 1: sero-epidemiological study);To identify the predictors of the occurrence of severe complications and to identify the prognostic factors for mortality (phase 2: clinical epidemiology);To analyze the healthcare pathways and patient experiences of management of COVID-19 in healthcare centers dedicated to SARS-CoV-2 infected patients, and to explore the perceptions, acceptability, and application of preventive strategies among the population (phase 3: socio-anthropological study).

Embracing all these problems, we developed the present project, whose overarching aim is to generate novel, pragmatic epidemiological and socio-anthropological data using robust scientific methods, to support Burkina Faso and guide policy in its fight against the COVID-19 pandemic.

To the best of our knowledge, this will be one of the first studies of this type to be performed in Sub-Saharan Africa since the emergence of COVID-19.

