### Inclusion criteria

All patients followed for COVID-19 (whether they are or were hospitalized or not), in the reference management centers cited above, or in outpatient care, in Ouagadougou and Bobo-Dioulasso.

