### Data collection and management

Socio-demographic and clinical data (age, gender, comorbidities, vital signs, biological parameters) at the time of diagnosis of COVID-19 will be recorded by the clinical research assistants in the COVID-19 management centers from the patients’ medical files and recorded in the CRF for the study (paper format) (Additional file 2). The development of severe complications (type of complication, date, outcome) will also be recorded in the CRF. In case of death, the date of death will also be recorded. For patients who recover, the end-date for survival analysis will be the date of discharge from the COVID-19 management center.

Data will be recorded in a secure, electronic database using the in-house Ennov software from the Georges-François Leclerc Cancer Centre (Dijon, France). Data will be monitored before locking the database. Data will be analyzed at the Georges-François Leclerc Cancer Centre.

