### Statistical analysis

Socio-demographic and clinical characteristics (age, gender, comorbidities, vital signs, biological parameters) of all patients at the time of diagnosis will be described and compared. Quantitative data will be described as mean ± SD or median (range). Qualitative variables will be described as number (percentage). Predictors of the occurrence of severe complications will be identified by logistic regression. The cohort will then be divided into two parts: the first part will be used to generate a score to predict severe complications (development set). The second part of the cohort will be used to validate the predictive score (validation set). The discriminatory capacity of the score will be assessed by the area under the receiver operating characteristic (ROC) curve (AUC), and the sensitivity, specificity, positive and negative predictive values of the score will be calculated. Prognostic factors of survival will be identified for the whole study population using Cox’s proportional hazards regression model. The outcome of interest will be death. Surviving patients will be censored at the date of discharge from the COVID-19 center. Imputation techniques and sensitivity analyses will be performed to account for missing data.

All analyses for phases 1 and 2 will be performed using STATA 14 (Copyright 1985–2015 StataCorp LLC; College Station, TX, USA) and R (www.r-project.org).

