## Discussion

### Communication and mobilization of the community

Given the nature of this study, and before the start of the sero-epidemiological (phase 1) and socio-anthropological (phase 3) components, we will openly dialogue with community leaders in the study zones. Through information to these leaders, to raise awareness about the positive repercussions of the study, we hope to ensure they will advocate for the study and convince the members of their communities to participate. Radio and/or television ads as well as public announcers with megaphones will also provide information to the public in the days prior to the researchers’ presence to collect data in the study zones. This widespread mobilization of the local community is key to achieving the inclusion and adherence necessary to guarantee the success of the study. In the general population, given that the blood draws will be performed in the participants’ homes, we plan to provide a small snack after the blood draw, comprised of a cold drink made of local fruit juices, and dry biscuits; these will be easy to handle without increasing the risk of contamination with SARS-CoV-2.

Participants in phase 2 (clinical epidemiology) who are hospitalized at the time of the study will receive written and oral information (patient information leaflet) about the study from a study investigator (physician). The information leaflet will outline the main objectives and procedures of the study and the expected risks and benefits. For participants who have difficulty understanding French, the written information will be complemented by oral information provided in the local language in the presence of a surrogate designated by the patient. For deceased patients, a request for exemption from the obligation to provide information will be submitted to the national ethics committee of Burkina Faso. The healthcare staff will try to contact as many recovered patients as possible to recover any data not available in the medical files, to ensure completeness of the CRFs, and minimize missing data. Recovered patients who accept to participate may come to the COVID-19 management center if they so desire to provide any data that is not available in the medical files. Their travel costs will be reimbursed in such cases.

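### Censoring survivors at discharge makes the phase 2 Cox model describe the daily death hazard among patients still under care, not the risk of death that the objective concerns

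*Protocol article*

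**What the plan says.** All of this is in the protocol article, under Phase 2: Clinical epidemiology unless noted.

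- **Model and event** (Statistical analysis): "Prognostic factors of survival will be identified for the whole study population using Cox’s proportional hazards regression model", and "The outcome of interest will be death".
- **Censoring** (Statistical analysis): "Surviving patients will be censored at the date of discharge from the COVID-19 center". Data collection and management gives the same rule and ties it to recovery: "For patients who recover, the end-date for survival analysis will be the date of discharge from the COVID-19 management center".
- **Target.** The specific objectives in the Background include, for this phase, "to identify the prognostic factors for mortality (phase 2: clinical epidemiology". Under Study endpoints, the second primary endpoint is the share of infected patients who die, with no limit at discharge.
- **Population** (Inclusion criteria): patients followed for COVID-19 "whether they are or were hospitalized or not".
- **Sensitivity analyses** (Statistical analysis): those named are for missing data only. Phase 2 mentions neither a competing-event method nor a fixed follow-up horizon.

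**The concern.** Patients leave the center alive because they have recovered, so the censoring time carries information about prognosis. Once discharge removes a patient from the risk set, the Cox hazard ratio compares death rates per day among those still under care. A factor that raises the risk of death and also lengthens stay spreads its extra deaths over more patient-days, so its daily rate may rise little, stay level or fall. A factor that only lengthens stay can look protective.

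Age, comorbidity and severity at diagnosis could plausibly act on both. This Cox model is the only analysis that the article specifies for mortality factors, so true prognostic factors could be missed or given the wrong direction, and factors with no effect on mortality could be flagged.

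A second gap is that the only end-date given for survivors is discharge from a center. The model covers the whole phase 2 population, which includes patients who were never hospitalised, and no end-date is stated for them.

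**Working it through.** **No plan figure to reproduce.** Phase 2 states no event count, effect size, mortality, length of stay or power. The one usable input is the anticipated minimum of 1,000 cases (Sample size calculation). Everything else below is assumed.

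**Set-up.** Assume constant daily hazards of death, d, and of discharge alive, r. The risk of death is m = d/(d + r), and the mean time under care is s = 1/(d + r). Hence d = m/s and r = (1 − m)/s.

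**What the planned model estimates.** With censoring at discharge, the Cox hazard ratio tends to the ratio of death hazards:

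HR = (m1/s1)/(m0/s0) = (risk ratio)/(ratio of mean stays).

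For m = 10% versus 20% (risk ratio 2.0):

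- stays 10 and 10 days: 0.020/0.010 = 2.0
- stays 10 and 15 days: 0.01333/0.010 = 1.33
- stays 10 and 20 days: 0.010/0.010 = 1.0
- stays 10 and 25 days: 0.008/0.010 = 0.8

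For m = 10% in both groups, stays 10 and 15 days: 0.00667/0.010 = 0.67.

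**Simulation check.** N = 1,000, half exposed, 400 replicates. The comparison analysis keeps patients discharged alive in the risk set beyond the last death.

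| Risk of death | Mean stay (days) | HR, censored at discharge | p < 0.05 | HR, survivors kept at risk | p < 0.05 |
|---|---|---|---|---|---|
| 5% vs 10% | 10 vs 10 | 2.02 | 84% | 2.07 | 84% |
| 5% vs 10% | 10 vs 15 | 1.33 | 18% | 2.03 | 85% |
| 5% vs 10% | 10 vs 20 | 1.00 | 3.5% | 2.04 | 86% |
| 10% vs 20% | 10 vs 15 | 1.35 | 36% | 2.11 | 99% |
| 10% vs 20% | 10 vs 20 | 1.00 | 5.5% | 2.07 | 98.5% |
| 10% vs 20% | 10 vs 25 | 0.80 | 23% | 2.06 | 98% |
| 10% vs 10% | 10 vs 15 | 0.67 | 52% | 0.98 | 6% |

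The equal-stay value for 10% versus 20% comes from the formula only. The simulated equal-stay row uses 5% versus 10%.

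**Reading.** With equal stays the two analyses agree. A stay half as long again attenuates a doubling of risk to about 1.35. Doubling the stay hides it, and a longer stay reverses it. In the last row, a factor with no effect on mortality is declared significant in about half of the runs.

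**The case against.** The strongest reply is that a Cox model that censors at a competing event is the standard estimator of the cause-specific hazard and needs no assumption about what would have happened after discharge. That is correct. A reader might infer that the model is invalid, and the documents do not support that. The defect is a mismatch: the article does not name the cause-specific hazard as its target, and its objective and endpoint point to the risk of death.

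Three further inferences are tempting and should be resisted.

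- **That the plan will overstate mortality.** Under the assumed rates (death 1% and discharge 9% per day), a Kaplan-Meier estimate censored at discharge would give 1 − exp(−0.28) = 24.4% at day 28, against a true 0.1 × (1 − exp(−2.8)) = 9.4%. Phase 2 announces no such curve. Mortality is reported as a simple proportion, which the censoring rule does not touch.
- **That non-hospitalised patients cannot enter the model.** The article does not show this. An end-of-follow-up date may be recorded on the case report form, which is not shown. What stands is that the article defines no end-date for them.
- **That planned contacts already supply vital status.** The Discussion says "The healthcare staff will try to contact as many recovered patients as possible", but this is a best-effort filling of gaps in medical files. It reaches people already classed as recovered, and those who answer are alive.

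It is also fair to say that the illustration is constructed. Full masking needs stay to lengthen in the same proportion as risk, and smaller differences only attenuate. The article gives no data to say which case applies.

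**Conclusion.** The point holds as a mismatch between the analysis and its stated purpose. The article itself fixes the event, the model and the censoring time, and repeats the end-date rule, so this is not a detail left to an unseen analysis plan.

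Under assumed constant hazards, the planned hazard ratio equals the risk ratio divided by the ratio of mean stays. A doubling of risk can therefore appear as anything from 2.0 to 0.8 as the stay ratio goes from 1 to 2.5. A factor without a mortality effect can appear as 0.67 at a stay ratio of 1.5. The direction of the argument does not depend on these inputs, but the size does.

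The effect is confined to the Cox analysis. Both primary endpoint proportions, the logistic regression for severe complications, and the score with its validation are unaffected.

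**What to change.** Amend Data collection and management and Statistical analysis in phase 2 so that the main mortality analysis targets the risk of death, in one of two ways:

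- treat discharge alive as a competing event, with cumulative incidence and a Fine-Gray model; or
- analyse death by a fixed horizon from diagnosis, keeping patients discharged alive at risk to that horizon.

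The two amount to the same thing when deaths after discharge are taken as absent. Report the discharge-censored Cox model as a secondary, cause-specific analysis and label it so. Apply the same horizon to non-hospitalised patients, which gives them a defined end-date.

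State the horizon in advance and make it long relative to the stays seen. In the 10 versus 20 day example, incidence by day 28 is 9.4% versus 0.2 × (1 − exp(−1.4)) = 15.1%, a ratio of 1.6 against 2.0 for eventual mortality.

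**Cost.** For admitted patients this is mainly a change of wording, because the date of death is recorded and the discharge date is already used. The price is that deaths after discharge count as absent unless they are learned of. A vital-status question at the recontact of recovered patients would capture them only partly and selectively, so this limit should be stated with the results.

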## Phase 3: Socio-anthropological study

The third and final phase of the study aims to analyze the healthcare pathway and the experiences of patients receiving care in dedicated centers for COVID-19 management in Burkina Faso, as well as the perceptions, acceptability, and application of preventive strategies in the population. An empirical study will be conducted in the COVID-19 management centers and in the community.

### Participant characteristics

For phase 3, sampling will take account of the different characteristics of the study zones and the population. The study will be performed in the cities of Ouagadougou and Bobo-Dioulasso, and four types of respondents will be included, namely:Persons who have recovered from COVID-19 after having been hospitalized in a specialized COVID-19 center. Eligible persons will be identified with help of the healthcare services;Relatives and/or caregivers (spouse, children etc.) of persons who have recovered from COVID-19 after having been treated in a specialized COVID-19 center;Healthcare professionals directly involved in the management of patients admitted to specialized COVID-19 centers (nurses, laboratory technicians, physicians);All-comers from the general population without known COVID-19 infection (men, women, young or old) in the cities of Ouagadougou and Bobo-Dioulasso.

For the choice of the study population, certain diversification criteria will be respected, to maximize heterogeneity, independently of the statistical frequency (young/old, men/women, city center/suburbs, nurses/laboratory technicians/physicians, high vs low level of education, etc.). The balance of these criteria will be verified as the study advances, during the daily and weekly updates. Similarly, the choice of the areas where the study will be carried out will aim to maximize the diversity of the different areas within both cities. The four following types of city area will be included: residential (central and peripheral), and poorer neighborhoods (central and peripheral). With four zones for each city, a total of eight zones will be included, as per the Table 1.

The choice of households will be at the discretion of the researcher in the field, according to the availability of persons to participate voluntarily in the study. The only restriction will be that the researchers must avoid including households who are already participating in the sero-epidemiological study, to avoid over-burdening the household members with research participation, and to prevent any influence of each study phase on the other.

### Inclusion criteria

Persons aged 18 years or older living in the cities of Ouagadougou or Bobo-Dioulasso:Who had received care for COVID-19 in one of the reference management centers, and who had recovered;Or a relative or caregiver (spouse, children etc.) Of such a person;Or a healthcare professional directly involved in the management of patients with COVID-19 in one of the reference management centers (nurses, laboratory technicians, physicians).

### Non-inclusion criteria

Persons who refuse to provide informed consent for study participation.

### Study endpoints

The endpoint for this study will be the acceptability and application of preventive strategies in the population.

### Sample size

For the sample size for phase 3, the principle of data saturation will be retained, i.e. the researchers will cease recruitment when it becomes clear that additional interviews and observations yield no new information either at individual or at group level. However, for the purposes of estimation, we aim to recruit around 100 persons altogether from the two cities. Persons who have recovered from COVID-19 infection will be identified via medical records by the medical staff, who will contact them to provide information about the study. The researcher will then contact the recovered patients thus identified, and invite them to participate in the study, and obtain the contact details of any relative or caregiver who could also be invited to participate. Healthcare professionals will be contacted directly in the COVID-19 management centers. Information about the study will be provided and their consent will be obtained. For the general population, researchers will recruit volunteers directly in their homes.

### Data collection and management

For this phase of the study, all persons who accept to participate (recovered patients, relatives/caregivers, medical staff) will be invited to participate in a semi-structured interview (Additional file 3) to explore their experience of COVID-19, treatment, the disease itself, their professional activity. Interviews will also explore perceptions, acceptability, and application of COVID-19 prevention strategies in the population.

### Analysis

Interviews will be recorded and complemented by observations made by the interviewer during the interview. Data will be transcribed and analyzed with the help of QDA Miner software.

## Discussion

### Communication and mobilization of the community

Given the nature of this study, and before the start of the sero-epidemiological (phase 1) and socio-anthropological (phase 3) components, we will openly dialogue with community leaders in the study zones. Through information to these leaders, to raise awareness about the positive repercussions of the study, we hope to ensure they will advocate for the study and convince the members of their communities to participate. Radio and/or television ads as well as public announcers with megaphones will also provide information to the public in the days prior to the researchers’ presence to collect data in the study zones. This widespread mobilization of the local community is key to achieving the inclusion and adherence necessary to guarantee the success of the study. In the general population, given that the blood draws will be performed in the participants’ homes, we plan to provide a small snack after the blood draw, comprised of a cold drink made of local fruit juices, and dry biscuits; these will be easy to handle without increasing the risk of contamination with SARS-CoV-2.

Participants in phase 2 (clinical epidemiology) who are hospitalized at the time of the study will receive written and oral information (patient information leaflet) about the study from a study investigator (physician). The information leaflet will outline the main objectives and procedures of the study and the expected risks and benefits. For participants who have difficulty understanding French, the written information will be complemented by oral information provided in the local language in the presence of a surrogate designated by the patient. For deceased patients, a request for exemption from the obligation to provide information will be submitted to the national ethics committee of Burkina Faso. The healthcare staff will try to contact as many recovered patients as possible to recover any data not available in the medical files, to ensure completeness of the CRFs, and minimize missing data. Recovered patients who accept to participate may come to the COVID-19 management center if they so desire to provide any data that is not available in the medical files. Their travel costs will be reimbursed in such cases.

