## Phase 2: Clinical epidemiology

The design of this clinical epidemiological phase of the study will comprise an ambispective analysis, involving first, a retrospective cohort of all patients with COVID-19 followed in one of the dedicated COVID-19 centers in the cities of Ouagadougou or Bobo-Dioulasso since the beginning of the epidemic; and second, prospective inclusion of all patients who present up until the end of the epidemic, or at the latest, 6 months after the start of the study. Retrospective data will be collected after study initiation, from the medical files of patients diagnosed since the start of the epidemic but before the study was initiated. These data will be used (if possible, depending on the number of cases collected) to construct a score to predict the occurrence of severe complications and death related to COVID-19, which could then be used to optimize patient management. The score will be validated in the prospective cohort to be included after study initiation.

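### Gaps in phase 2 files are filled by contacting recovered patients, with no equivalent for deaths, so recallable predictors of mortality may be more complete in survivors

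*Protocol article*

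**What the plan says.** All references are to the Protocol article.

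- **Source of predictors, all patients** (Phase 2, Data collection and management): "Socio-demographic and clinical data (age, gender, comorbidities, vital signs, biological parameters) at the time of diagnosis of COVID-19 will be recorded". The same sentence says that these data "will be recorded by the clinical research assistants in the COVID-19 management centers from the patients’ medical files".
- **Retrospective cohort** (Phase 2: Clinical epidemiology): "Retrospective data will be collected after study initiation, from the medical files of patients diagnosed since the start of the epidemic". These data are intended for building the score.
- **Second source, recovered patients** (Discussion, Communication and mobilization of the community): "The healthcare staff will try to contact as many recovered patients as possible to recover any data not available in the medical files". The route is voluntary: "Recovered patients who accept to participate may come to the COVID-19 management center if they so desire to provide any data" that the files lack, with travel reimbursed.
- **Deceased patients** (same section): "For deceased patients, a request for exemption from the obligation to provide information will be submitted to the national ethics committee of Burkina Faso". Nothing is said there about recovering their missing data from relatives or anyone else.
- **Analysis** (Phase 2, Statistical analysis): death is modelled by Cox regression in the whole cohort, and severe complications by logistic regression and a score. On missing data: "Imputation techniques and sensitivity analyses will be performed to account for missing data". The article does not connect that sentence to the recovery step.

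**The concern.** The recovery step is meant to reduce missing data, and in itself that is sound. The difficulty is that the group it reaches is defined by the outcome. A comorbidity missing from a survivor's file may be supplied later. The same gap in the file of a patient who died has no described way of being filled. Completeness of the exposure can then depend on the outcome being modelled.

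Death is one of the two primary endpoints of phase 2, and finding prognostic factors for mortality is part of its stated objective. If recorded comorbidity rises in survivors but not in deaths, a moderate risk factor can lose its association with death or appear protective. The retrospective files are where gaps and later contact are likely to matter most. Once recalled and file values are merged in the CRF without a marker, no later analysis can separate them.

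**Working it through.** The article gives no prevalence, missing-data rate, capture rate or effect size for phase 2, so there is no planned figure to reproduce. Every rate below is an assumption.

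**1. Blanks entered as absent.** Let p0 be the true prevalence in survivors and p1 that in deaths, with p1/(1−p1) = OR × p0/(1−p0). Let c1 and c0 be the fractions of true carriers recorded in deaths and in survivors. Then

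observed OR = [p1c1/(1−p1c1)] / [p0c0/(1−p0c0)].

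Take p0 = 0.25, true OR = 2.0, c1 = 0.70 (file only) and c0 = 0.95 (file plus contact):
- odds in deaths = 0.333 × 2 = 0.667, so p1 = 0.40
- deaths: 0.40 × 0.70 = 0.28, and 0.28/0.72 = 0.389
- survivors: 0.25 × 0.95 = 0.2375, and 0.2375/0.7625 = 0.311
- observed OR = 0.389/0.311 = 1.25

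| Capture, deaths / survivors | True 2.0 | True 1.5 | True 1.0 |
|---|---|---|---|
| 70% / 95% | 1.25 | 0.98 | 0.68 |
| 70% / 70% (file only in both) | 1.83 | 1.43 | 1.00 |
| 80% / 95% | 1.51 | – | – |
| 80% / 80% (file only in both) | 1.88 | – | – |
| 90% / 95% | 1.81 | – | 0.93 |

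Equal under-recording attenuates mildly. The asymmetry does the damage, and it shrinks quickly as the files improve.

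A second scenario agrees: prevalence 20% in survivors, 40% file gaps, 80% of survivors' gaps recovered. A true OR of 2.0 gives 1.11 and 1.5 gives 0.87. Over gaps of 10% to 50% and recovery of 50% to 100%, a true OR of 3 never fell below 1.09, so strong factors keep their direction.

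**2. Blanks kept as missing, gaps unrelated to the predictor.** This was simulated as a Cox analysis with 1,000 patients, 300 replicates, about 9–10% deaths, prevalence 20%, 40% file gaps and 80% of survivors' gaps recovered.

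| Handling | True HR 2.0 | True HR 1.5 |
|---|---|---|
| Complete case | 2.00 | 1.49 |
| Imputation including the outcome | 1.97 | 1.46 |
| Imputation omitting the outcome | 1.58 | 1.31 |
| Blank entered as absent | 1.15 | 0.90 |

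**3. Blanks kept as missing, file recording depends on the predictor.** Let a1 and a0 be the probabilities that the item is recorded in the file for carriers and non-carriers, and r the fraction of survivors' gaps recovered. The complete-case OR is

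true OR × (a1/a0) / {[a1+(1−a1)r] / [a0+(1−a0)r]}.

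- Carriers recorded less often (a1 = 0.5, a0 = 0.8, r = 0.8): 2.0 × 0.625/(0.90/0.96) = 1.33, and a true 1.5 gives 1.00.
- Carriers recorded more often (a1 = 0.8, a0 = 0.6, r = 0.8): 2.0 × 1.333/(0.96/0.92) = 2.56, away from the null.
- With r = 0 the two ratios cancel and the true OR returns. This is the case for a file-only analysis, provided that file recording follows the same pattern in survivors and deaths.

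**4. Severe-complication outcome.** Patients who survive a complication are also contacted. If half of complicated patients survive (assumption), and all others do, average capture in cases is (0.70 + 0.95)/2 = 0.825, against 0.95 in non-cases. A true OR of 2.0 gives 0.40 × 0.825 = 0.33, then (0.33/0.67)/0.311 = 1.58. A true 1.5 gives 1.22. The corresponding mortality figures are 1.25 and 0.98.

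**The case against.** The strongest reply is that no sentence in the article says an unmentioned item will be entered as absent. The recovery step itself speaks of unavailable and missing data, the analysis section plans imputation, and the CRF (an additional file, not shown) may offer an unknown option. If blanks are treated as missing, missingness that depends on an observed outcome can be handled by imputation, as step 2 shows. This stands. A reader might infer that the planned imputation cannot repair the problem; the documents do not support that. What remains is that imputation helps only if blanks are kept as missing, works best with the outcome in the model, and does not by itself resolve step 3.

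Other points also limit the concern:
- Saying that recovered patients are the only source is an inference from silence about the deceased, although the article treats the deceased in the same paragraph and describes no data recovery for them.
- A reader might take all diagnosis-time predictors to be affected. Vital signs and laboratory values are unlikely to be recovered by interview, so the exposure is mainly comorbidities and history.
- Details of the imputation model can properly sit in an analysis plan that is not shown. The source of each value is different, because it has to be captured when the data are collected.

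**Conclusion.** The point holds in conditional form. The article describes data recovery for recovered patients and nothing equivalent for deaths, and it models death in the combined cohort. Completeness of recallable predictors may therefore differ by a primary outcome.

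The size depends on data entry. With blanks entered as absent, a true OR of 2.0 falls to between 1.25 and 1.81 across the 25%-prevalence scenarios with unequal capture, and a true 1.5 reaches 0.98 at 70% against 95% capture. With blanks kept as missing and gaps unrelated to the predictor, bias is negligible under imputation with the outcome or complete-case analysis. Imputation without the outcome attenuates but did not reverse the effect.

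Two stronger conclusions might be drawn and are not supported. One is that estimates will generally be biased downward: when carriers are better recorded in files, the bias goes upward (2.56 for a true 2.0). The other is that the severe-complication score is distorted to the same degree: survivors of complications are contacted too, so the effect there is smaller.

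**What to change.** Before data collection:

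1. Add a CRF field giving the source, medical file or later contact, of each recallable predictor.
2. Enter items that the file does not mention as unknown, never as absent.
3. State that the imputation model for phase 2 includes the outcome (for the Cox analysis, death status and follow-up time).
4. Prespecify a mortality analysis that uses only values documented in the file at diagnosis, with gaps handled identically in survivors and deaths, and report it beside the analysis that includes recovered data.

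Making the file-only analysis the sole primary analysis is not required. It would discard valid information, and that trade-off is for the investigators to judge.

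The cost is one extra CRF field per item, one extra analysis, and more missing values among survivors in the file-only analysis. The source field cannot easily be reconstructed once collection is over.
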